Key clinical outcome measures will be performed at 8-week intervals throughout the study. Additional clinical outcome measures will be assessed at baseline and at 9 months.

PET will be performed at baseline (after randomisation but before the first infusion with study drug) and 9 months in all randomised subjects. Additional 3-month scans will be obtained from subjects randomised during the Pilot Stage.

In order to minimise any potential placebo effect, educational videos for staff, caregivers, and subjects will be reviewed at the beginning of the consent process. These videos are designed to encourage equipoise by emphasizing the concept of a “research partnership” rather than generating expectations of therapeutic benefit and to educate subjects on their role as a clinical trial subject. In addition, the consenting process will be scripted in an effort to standardize its administration and minimise the potential for the introduction of bias.

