Coma Scale) will also be done before infusion, 30 minutes into the infusion, and after completion of the infusion.

Final T2-weighted and FLAIR 3T MRI scans will be completed within 2 hours of the test infusion. These latter scans will be relevant to determine infusate distribution as part of the post-surgery eligibility assessment (Section 5.3.4).

**Primary Study Stage subjects:** The test infusion of aCSF will contain gadolinium contrast and be followed within 2 hours by T2-weighted, FLAIR and T1-weighted 3T MRI scans to assess catheter patency and infusate distribution. Subjects will be carefully observed for safety during and after administration of the test infusion. During administration, seated vital signs (systolic and diastolic BP, HR and RR) will be collected every 15 minutes, and both seated and standing systolic and diastolic BP and HR will be assessed within 30 minutes after the end of the infusion. A brief neurological screen (Glasgow Coma Scale) will also be done before infusion, 30 minutes into the infusion, and after completion of the infusion.

Subjects randomised in the Pilot Stage will remain at the facility for safety observation for at least 22 hours (i.e., including an overnight stay) after completing the test infusion. Subjects randomised in the Primary Study Stage will be observed for at least 4-6 hours prior to discharge home.

The post-test infusion MRI will be reviewed for the post-surgery eligibility assessment. Subjects who are deemed to have adequate catheter function yielding at least 40% volume coverage of a predefined volume of interest (posterior two thirds of the dorsal half of the putamen) in each putamen will be randomised and will return for their first treatment after approximately 4 weeks. Corrective action will be considered for subjects who have insufficient catheter performance yielding less than 40% volume coverage of a predefined volume of interest (posterior two thirds of the dorsal half of the putamen) in each putamen. This may include the following:

- Increasing the infusion volume for any given catheter to compensate for loss or inability to use the second catheter in the same putamen. The total infusion volume given per putamen must not exceed that given in the standard regimen. The tolerability of an alternate infusion regimen and its ability to provide sufficient putamenal coverage would need to be confirmed using another infusion of aCSF with following MRI prior to proceeding with study drug

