infusions. Approximately 4 weeks will be allowed between different test infusions and between the last test infusion and the first study infusion.

- Surgical replacement of blocking or leaking catheters: In case of surgical correction, another 4-week healing period, followed by renewed assessment of catheter performance, will be allowed.

In addition, MoCA (Section 5.7.2.1) will be performed in the ON state on the day of the test infusion, to assess any cognitive effects of the surgery. This must be completed prior to infusion of diluent.

Also during this visit, subject PD fluctuation diaries will be distributed and the subject will be instructed to complete the diaries on 3 successive predetermined days in the week prior to the next study visit.

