#### **5.5.4 Randomisation and Preparation of Study Drug**

Randomisation will be administered centrally via the Bristol Randomised Trials Collaboration (BRTC) Clinical Trials Unit (CTU) after the inclusion/exclusion criteria have been confirmed and the post-surgery randomisation criteria are met as confirmed by the PI. Eligible subjects in the Pilot Stage will be randomised in a 2:1 ratio to achieve 4 active and 2 placebo subjects. In the Primary Study Stage, eligible subjects will be randomised in a 1:1 ratio to the active or placebo arm, using a blocked randomisation scheme with a block size of 6. The randomisation sequence will be based on a computer programme, which will allocate a random number that determines the study drug (GDNF or aCSF) dispensed by the pharmacy whilst maintaining concealment of allocation.

All study drug will be prepared by an unblinded pharmacist at the study site based on the randomisation. Ready to use preparations of GDNF or aCSF will be provided to the PI or designee in identical containers identifiable only by codes unknown to the PI or any other study staff. Drug preparation guidelines are provided in a separate pharmacy manual.

In the event that there is a delay in randomization which results in the baseline assessment occurring more than 24 weeks after screening visit 2, efficacy outcome measures completed during screening but not repeated at baseline must be repeated

prior to the baseline visit unless they have a significant practice effect. The list of measures to be repeated includes:

- Stroop
- Reaction time
- FrSBe
- UPPS-P
- PD NMSS
- PDQ-39
- EQ-5D
- SNAQ
- UPSIT
- QUIP

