### **5.6.1 Baseline and First Treatment (Week 0)**

As part of the baseline assessments, all subjects will undergo PET scanning between randomisation and the first infusion with study drug.

The subject will report to the investigative centre (PI or designee) for baseline assessments and to begin treatment.

For this assessment, subjects will withhold all PD medications as follows:

- No PD medications will be taken after 6:00 PM on the night before the Baseline assessments and
- No long-acting PD medications will be taken on the day before the Baseline assessments.

Subjects will refrain from eating any high-protein foods on the morning of the assessments.

At the beginning of the assessment, all OFF period measures are to be completed first:

- UPDRS part II (ADL) and part III (motor) in OFF-state (Section 5.7.1.1)
- Timed walking test (Section 5.7.1.2)
- Timed tapping test (Section 5.7.1.3)

A levodopa challenge will then be performed (refer to study-specific Standard Operating Procedures) and when the subject goes ON the following post-challenge tests will be performed:

- Full UPDRS (including parts I, II, III and IV; Section 5.7.1.1)
- Timed walking test (Section 5.7.1.2)
- Timed tapping test (Section 5.7.1.3)
- QUIP (Section 5.7.2.6)

Additional pretreatment assessments which can be completed irrespective of ON/OFF status will include the following:

- Weight and height.

- Vital signs: Seated systolic and diastolic BP, HR, RR and temperature will be assessed after the subject has been sitting quietly for at least 5 minutes. Standing systolic and diastolic BP and HR will also be assessed after the subject has been standing for 3 minutes.
- Collection of subject PD fluctuation diaries (Section 5.7.1.4)
- Any changes to concomitant medications from the previous visit will be recorded. All over-the-counter or prescription medications, vitamins, and/or herbal supplements will be recorded in the CRF with their indications.
- Any AEs observed or reported since the previous visit will be recorded.

After completion of the pretreatment procedures and assessments, the unblinded pharmacist will provide blinded study drug to the PI or designee, who will administer the drug over a period of approximately 90 to 150 minutes using pre-programmed micro-infusion pumps (detailed in Sections 6.2 and 6.3).

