### **6.2.2 Drug Infusions**

The drug administration system comprises 4 programmable syringe pumps, four 5-mL Plastipak syringes (Becton Dickinson), 4 sealed extension lines with male Luer attachments (each containing a septum) at one end, 4 double-sided syringe connectors with female Luer attachments (each holding an internal needle), 4 lengths of sealed drug administration tubing with male Luer attachments (each containing a septum) at both ends and a 4-channelled drug administration set. The latter comprises 4 needles mounted in a hub, each connected to independent bacteria and bubble filters and thence to short lengths of tubing, each with a female Luer attachment holding an internal needle. In addition, 3 syringe connectors with female Luer attachments at both ends and holding an internal needle at one end are used by the pharmacist preparing the study drug to fill the sealed extension lines and sealed drug administration lines.

Prior to drug administration, the pharmacist will fill the 4 lengths of drug administration tubing with an appropriate dose of drug (using 2 syringe connectors, one at each end of the sealed tubing), and label each line appropriately without identifying the treatment allocation. The pharmacist will further fill 4 syringes with aCSF, connect them to the open ends of the extension lines and fill the extension lines (using a single syringe connector at the opposite end to evacuate air). All syringe connectors will be disconnected and discarded once all lines have been filled. The filling of devices will take place up to 48 hours before a planned drug infusion.

For the infusion, each syringe/sealed extension line assembly will be connected to a double-sided-syringe connector, then to a drug administration line, then to one of the 4 channels of the drug administration set which prior to this has been flushed with aCSF.

Connection of the drug administration set to the port begins with the health professional cleaning the port and the immediate surrounds with an aseptic technique. The cylindrical needle hub of the drug administration set will be positioned over the port and locked to the port using a socket screw key. The 4 needles will be lowered through the port septum by use of a hand-tightened nut and thence individually guided into their separate channels that conduct the drug to identifiable catheters.

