| RT                                                      |                |   |                | X              |                 |    | X               |    |                 |    | X               |
| Verbal fluency                                          |                |   |                |                |                 |    |                 |    |                 |    | X               |
| SNAQ                                                    |                |   |                |                |                 |    |                 |    |                 |    | X               |
| UPSIT                                                   |                |   |                |                |                 |    |                 |    |                 |    | X               |
| NMSS                                                    |                |   |                | X              |                 |    | X               |    |                 |    | X               |
| BDI                                                     |                |   |                |                |                 |    |                 |    |                 |    | X               |
| QUIP                                                    | X              |   | X              |                | X               |    | X               |    | X               |    | X               |
| Collect PD fluctuation diaries                          | X              |   | X              |                | X               |    | X               |    | X               |    | X               |
| Dispense PD fluctuation diaries                         |                | X |                | X              |                 | X  |                 | X  |                 | X  |                 |
| Randomization                                           | X              |   |                |                |                 |    |                 |    |                 |    |                 |
| Infusion of study drug                                  | X              | X | X              | X              | X               | X  | X               | X  | X               | X  |                 |
| Glasgow Coma Scale j                         | X              | X | X              | X              | X               | X  | X               | X  | X               | X  | X               |

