| Adverse events k                             | X              | X | X              | X              | X               | X  | X               | X  | X               | X  | X               |
| Concomitant medications l                    | X              | X | X              | X              | X               | X  | X               | X  | X               | X  | X               |

- a T2-weighted and FLAIR 3T MRI; are to be completed within 2 hours of study drug infusion in Pilot Stage subjects at all time points. Also, Pilot Stage subjects will be receiving the Week 0 infusion in the MRI suite to allow for additional real-time MR imaging.
- b T1-weighted as well as T2-weighted and FLAIR 3T MRI scans; are to be completed within 2 hours of a gadolinium contrast-containing test infusion of diluent at Week 40 ( $\pm 1$  week). No interim T2-weighted or FLAIR MRI monitoring will be done in Primary Study Stage subjects unless clinically mandated.
- c At Weeks 0, 8, 16, 24, 32 and 40, no PD medications will be taken after 6:00 PM on the night before the assessments and no long-acting PD medications will be taken on the day before the assessments. Subjects will refrain from eating any high-protein foods on the morning of the assessments.

- d The Week 0 PET may be performed any time after randomisation and before the first infusion with study drug.
- e Subjects randomised during the Pilot Stage only.
- f The Week 40 PET may be performed at any time in the two weeks prior to Week 40.
- g Seated systolic and diastolic BP, HR, RR and temperature will be assessed after the subject has been sitting quietly for at least 5 minutes. Standing systolic and diastolic BP and HR will also be assessed after the subject has been standing for 3 minutes. During drug administration, seated vital signs (systolic and diastolic BP, HR and RR) will be collected every 15 minutes during the first infusion in any subject and every 30 minutes during subsequent infusions, and both seated and standing systolic and diastolic BP and HR will be assessed within 30 minutes after the end of the infusion.
- h Brief physical examination, targeted, at the Investigator's discretion, to identify changes from Screening Visit 1.

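### Randomisation is placed about 4 weeks before the first infusion in the text but at Week 0 in Table 2; the text's timing lets never-treated subjects without a Week 0 baseline into the ITT set

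*Protocol*

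**What the plan says.** **Time of randomisation, text.** Under Section 5.5.3, subjects whose test-infusion MRI shows adequate catheter function "will be randomised and will return for their first treatment after approximately 4 weeks". The same section, dealing with corrective action, states the interval again: "Approximately 4 weeks will be allowed between different test infusions and between the last test infusion and the first study infusion". Section 5.5.4 triggers allocation "after the inclusion/exclusion criteria have been confirmed and the post-surgery randomisation criteria are met as confirmed by the PI"; it requires neither a baseline score nor a check on the day of dosing.

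**Time of randomisation, PET wording.** Section 5.5: "PET will be performed at baseline (after randomisation but before the first infusion with study drug". Section 5.6.1: "all subjects will undergo PET scanning between randomisation and the first infusion with study drug". Table 2, footnote d: "The Week 0 PET may be performed any time after randomisation and before the first infusion with study drug". All three assume an interval between allocation and first dose.

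**Time of randomisation, table.** In Table 2 the row "Randomization" is marked under Week 0 only and carries no footnote. Table 1, which covers the test-infusion visit, has no such row.

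**Baseline and analysis set.** Section 5.6.1 takes the baseline OFF motor UPDRS at the Week 0 visit, before the first infusion. Sections 5.2.1 and 5.7.1.1 define the primary endpoint as a percentage change from that score, and Section 8.1 also uses it as the covariate. Section 8.7 puts every randomised Primary Study Stage subject in the primary ITT set, whatever treatment was received. The two treated-subject safety populations in that section require at least one dose; the ITT set does not.

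**The concern.** Two readers of this protocol could randomise about 4 weeks apart: one follows Section 5.5.3, the other follows the schedule table.

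If the text is followed, the score that defines the primary endpoint is measured after allocation. Subjects at this stage have recently had catheters and a skull-mounted port implanted. One who withdraws, has an adverse event or becomes ineligible before Week 0 is already randomised. That subject counts in the ITT set but has never been dosed and has no Week 0 score. The percentage change then has no denominator and the model has no covariate value. Section 8.2 describes its 5% allowance on the footing that earlier scores are carried forward, and that gives nothing to work with when the baseline itself was not taken.

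In a 36-subject trial this is missing data that the timing of allocation creates and could largely avoid.

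**Working it through.** **1. Is a gap planned?** Section 5.5.3 links allocation to the test-infusion MRI and puts first treatment about 4 weeks later. The PET wording in three places needs a non-zero interval. Section 5.5.4 also speaks of a late randomisation pushing back the baseline assessment, which again puts allocation first. Only the Table 2 row points to Week 0. No section fixes an exact day, so about 4 weeks is the plain reading of Section 5.5.3 and not a stated visit window.

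**2. The plan's own sample size.** Inputs from Section 8.2: difference 20 points, SD 20, two-sided alpha 0.05, power 80%, 1:1 allocation, 34 evaluable, 5% loss, 36 randomised.

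Two-sample t test, noncentrality = difference / (SD × √(1/n₁ + 1/n₂)). With 17 per arm this is 20 / (20 × √(2/17)) = √8.5 = 2.92 on 32 degrees of freedom, and power is 80.7%. With 16 per arm it is 78.1%. So 17 per arm, 34 in total, reproduces the plan.

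Inflation: 34 / 0.95 = 35.8, rounded up to 36. This also reproduces.

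Allowance: 36 − 34 = 2 subjects (2/36 = 5.6%).

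**3. Power by total number lost, same formula.**

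| Lost | Spread over both arms | All from one arm |
|---|---|---|
| 0 | 83.0% (18/18) | – |
| 1 | – | 81.9% (18/17) |
| 2 | 80.7% (17/17) | 80.6% (18/16) |
| 3 | 79.4% (17/16) | 79.1% (18/15) |
| 4 | 78.1% (16/16) | 77.5% (18/14) |

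Each loss costs roughly 1 to 1.5 points; the last one-arm step is 79.1 − 77.5 = 1.6.

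**4. How often might it happen?** The documents give no rate, so p below is an assumption. With 36 randomised, the chance of at least one gap loss is 1 − (1 − p)³⁶, and the chance of three or more is the binomial tail.

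| Assumed p | At least 1 | 3 or more |
|---|---|---|
| 1% | 30.4% | 0.6% |
| 2% | 51.7% | 3.5% |
| 5% | 84.2% | 26.8% |
| 10% | 97.7% | 71.2% |

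Even at 2%, at least one ITT subject without a Week 0 baseline is about as likely as not. Gap losses alone exceed the allowance of 2 only if p is well above that.

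**The case against.** **On the contradiction.** Table 2 columns are nominal visits that also hold off-day procedures: the Week 0 PET may fall before the visit, and the Week 40 PET up to two weeks before. With no randomisation row in Table 1, Week 0 is the natural column, and the body text agrees with itself that allocation precedes dosing. This is fair, and it makes the conflict one of scheduling. But the PET rows carry footnotes that release them from the visit day, and the randomisation row does not.

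**On the missing baseline.** A reader might infer that the ITT analysis becomes impossible. The protocol does not support that. An OFF motor score is taken at Screening Visit 2, Section 8.1 foresees sensitivity analyses with other baseline values, and Sections 5.6.5 and 5.10 ask subjects who stop early to complete the Week 40 assessments where they will. Section 8.5 leaves missing data to the SAP. So a gap loss may have a screening score and a later score, and how to use them is for the SAP. What stands is narrower: the primary endpoint as defined, from the Week 0 score, cannot be computed for that subject.

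**On power.** A reader might infer that the trial falls below 80%. The 78.1% figure needs four losses, so two gap losses would have to be joined by two more that have nothing to do with the timing of allocation. One or two gap losses alone do not bring it there. Section 8.2's carry-forward premise also means that many on-treatment dropouts would not count as lost, and the planned MMRM uses their partial data. Absorbing a gap loss is then arguably what the allowance is for.

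**On feasibility.** A reader might infer from "The filling of devices will take place up to 48 hours before a planned drug infusion" that no lead time is needed. That sentence sets a maximum interval. It does not show that four drug lines can be filled within the assessment visit, and the preparation guidelines are in a separate pharmacy manual. This objection stands and shapes the fix.

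**Conclusion.** The point holds as a reconciliation and a modest design improvement. The text and Table 2 give different times for randomisation and must be brought into line. Under the text, a subject lost before Week 0 is in the primary ITT set with no dose and no Week 0 baseline.

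The sample size is correct as stated, and the loss of power is small: still about 80.6% or more with one or two gap losses, slightly below 80% from a third loss of any kind. With allocation concealed and no drug yet given, such losses should not depend on treatment, so the cost is precision and an unclear analysis set, not bias.

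This rests on the plain reading of Section 5.5.3, on a t test standing in for the MMRM, and on losses that contribute nothing to the primary comparison.

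**What to change.** State one time of randomisation in Sections 5.5.3 and 5.5.4 and in Table 2. Confirm post-surgery eligibility after the test infusion, as now, but request the allocation as close to the first infusion as drug preparation allows. One workable form is to allocate inside the 48-hour line-filling window of Section 6.2.2 and, where the visit spans more than one day (Section 5.6 permits this if necessary), after the baseline OFF UPDRS. Where same-day preparation forces allocation before the score, the gap still shrinks from about 4 weeks to at most two days.

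In Sections 5.5 and 5.6.1 and in footnote d of Table 2, tie the baseline PET to confirmed post-surgery eligibility instead of to randomisation. Otherwise the PET wording keeps allocation early.

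The cost is an amendment to the wording, tighter pharmacy timing around Week 0, and an occasional subject who has a baseline PET and is then not randomised. No change to the 36 is needed.
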